### Inclusion and exclusion criteria

The inclusion and exclusion criteria of the study are shown in Table 2.

**Table 2 Tab2:** Overview of the study's inclusion and exclusion criteria: Pronounced aphasia is defined as severe communication impairment that limits participation in or comprehension of study-related assessments. In cases of suspected speech disorder, a diagnostic evaluation will be performed using the modified Aachen Aphasia Test, the Aachen Aphasia Bedside Test, and the Aphasia Check List. Abbreviations: CNS = central nervous system; WHO = World Health Organization; IDH = isocitrate dehydrogenase; ICU = intensive care unit

Inclusion criteria	Exclusion criteria
At least 18 years of age	Presence of Neurodegenerative diseases (e.g. Parkinson's disease, Alzheimer's disease, Huntington's disease, Korsakoff's syndrome, Pick's disease, Shy-Drager syndrome)
Newly-diagnosed glioblastoma (CNS WHO 2021; IDH wild-type) before start of first radiotherapy	History of invasive tumors or surgery in the head or neck area, except for surgeries for non-invasive skin tumors (e.g. basal cell carcinomas)
Never received prior chemotherapy	Permanent olfactory impairment following infections (e.g., influenza, coronavirus)
Never received radiotherapy to the head or neck before	Conditions that, in the examiner’s judgment, could interfere with the participant’s study compliance (e.g., schizophrenia)
KPS ≥ 70	Language barriers likely to interfere with participation or comprehension of study procedures
No history of severe head or brain trauma requiring ICU admission or classified as Glasgow Coma Scale grade 3	
No respiratory infection at the time of inclusion	
No significant aphasia	

### Study procedures

#### Study visits

Study visits for glioblastoma patients will be scheduled as follows: screening (postoperative, once histology is available), baseline (as soon as MGMT promoter methylation status is determined, but before radiotherapy), visit 1 (4 ± 1 weeks after radiotherapy ends and before adjuvant chemotherapy begins), visit 2 (3 months ± 2 weeks after end of radiotherapy), visit 3 (6 months ± 2 weeks after end of radiotherapy), visit 4 (12 months ± 2 weeks after end of radiotherapy), and follow-up visits (every 6 months ± 2 weeks after visit 4, for a maximum of 2 years).

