Therefore, this prospective, multicenter study aims to determine whether olfactory dysfunction can serve as an independent prognostic marker for glioblastoma outcomes when controlling for known confounders and following patients longitudinally. The hypothesis is that the disturbance of olfactory function is intrinsically caused by the disease itself and not by external factors such as radiochemotherapy or tumor infiltration in structures of the olfactory tract.

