#### Investigation of the olfactory sense

The extended Burghart test comprises a threshold and an identification module for detailed olfactory assessment [11]. The threshold test includes 16 dilutions of an odorant (plus blanks), presented in triplets; correct and incorrect choices guide up- or downgrading the dilution level until a consistent threshold is found (score range 1–16). Higher scores indicate a better ability to detect weak odors. The identification test features 16 possible smells, with 12 randomly selected at each test; participants choose the correct smell from four options. Each correct answer scores 1 point (maximum 12). Testing each nostril separately, average scores ≥ 10 classify as normosmia, < 10 as hyposmia.

During screening, only the identification test is performed to assign participants to the normosmia or hyposmia group. At subsequent visits, both threshold and identification modules are done. The threshold test is carried out with both nostrils simultaneously, starting at dilution 16. Participants must avoid eating, drinking, smoking, or chewing gum for at least 15 min before testing. Correct answers are not revealed to maintain test reliability across repeated assessments.

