#### MRI

All MRIs are used as part of clinical routine at the following points in time: Postoperative (24 h-72 h post surgery), before starting adjuvant chemotherapy (≈4 weeks post-radiotherapy), and approximately 3, 6, 12, 18, and 24 months after radiotherapy. The first post-radiotherapy MRI will be used to determine whether the tumor infiltrates the olfactory tract. A high-resolution coronal T2 sequence is required for this purpose. Two radiologists at independent centers will evaluate all MRIs. In contrast to the local radiologist, the reference radiologist is blinded to the patient's sex, name, and year of birth. Additionally, both radiologists are blinded to each other's assessment regarding olfactory tract infiltration on the MRI. In selected patients, a DTI (diffusion tensor imaging) sequence will be obtained for a more precise assessment of infiltration in olfactory regions.

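### Hyposmia is first assessed after surgery, and no stated variable shows whether the operation injured an olfactory structure, so surgical hyposmia could be read as intrinsic to the disease

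*Protocol article*

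**What the plan says.** **Timing and grouping.** Under Study visits, the first visit is "screening (postoperative, once histology is available". Table 1 begins at that visit, and no preoperative smell test is described. Under Investigation of the olfactory sense: "During screening, only the identification test is performed to assign participants to the normosmia or hyposmia group". The rule uses the score only: "average scores ≥ 10 classify as normosmia, < 10 as hyposmia".

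**Imaging.** The MRI section lists a routine early scan, "Postoperative (24 h-72 h post surgery", and states that "Two radiologists at independent centers will evaluate all MRIs". The one olfactory reading it defines is on a later scan: "The first post-radiotherapy MRI will be used to determine whether the tumor infiltrates the olfactory tract". The Stratification section says the same.

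**Surgery as a variable.** Extent of resection is a stratification factor (Study cohort) and a planned covariate (Sample size calculation and sampling strategy). It is absent from the covariates listed under Statistics.

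**Aim.** The Introduction hypothesises that the disturbance is "intrinsically caused by the disease itself and not by external factors such as radiochemotherapy or tumor infiltration in structures of the olfactory tract". The Perspective section repeats this as something to be proved and names two mechanisms to be tested: tumour invasion, and neurotoxicity from radiotherapy or chemotherapy.

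**The concern.** An operation precedes every smell test in the study, yet surgical injury is not among the alternative explanations examined. A resection that removes or damages a structure serving smell could lower the score. If no tumour is visible there after radiotherapy, the patient is recorded as hyposmic without infiltration, and that is the pattern on which the claim of intrinsic dysfunction would rest.

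The choice of scan adds a second route to the same cell. A structure that was infiltrated and then resected may be read as not infiltrated on the post-radiotherapy MRI.

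Nothing else in the stated design separates these cases. The controls are healthy and not operated on for glioblastoma. Serial testing starts after surgery, so it can show change during radiochemotherapy but not change caused by the operation. Extent of resection says how much tumour was taken, not from where: two complete resections score alike whether or not one of them passed through an olfactory region.

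**Working it through.** **1. What each stated variable can detect**

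| Possible cause of a low score | Stated item that could reveal it |
|---|---|
| Tumour in the olfactory tract | Infiltration reading, first post-radiotherapy MRI |
| Radiotherapy or chemotherapy | Screening and baseline tests compared with visit 1 onwards |
| Age-related decline | Matched healthy controls |
| Surgical injury to an olfactory structure | None; extent of resection is at best a weak proxy |

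The article itself gives grounds for the last row. The Introduction lists surgical resection among the tumour therapies and counts side effects of such therapies among possible explanations for olfactory dysfunction.

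**2. Possible effect on the survival hazard ratio (illustration)**

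Inputs: HR 0.43 for normosmia versus hyposmia (Sample size section). The share *s* of hyposmic patients whose hyposmia is surgical is assumed, because the article gives no figure. Let *r* be the hazard of those patients relative to the other hyposmic patients. The average-hazard approximation is

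observed HR = 0.43 / [(1 − s) + s × r].

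If these patients carry the normosmia hazard, r = 0.43:

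- s = 10%: 0.43 / (0.90 + 0.043) = 0.43 / 0.943 = 0.46
- s = 20%: 0.43 / (0.80 + 0.086) = 0.43 / 0.886 = 0.49
- s = 30%: 0.43 / (0.70 + 0.129) = 0.43 / 0.829 = 0.52

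On the log scale, ln 0.43 = −0.844. The losses are −ln 0.943 / 0.844 = 7%, −ln 0.886 / 0.844 = 14% and −ln 0.829 / 0.844 = 22%.

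A simulated Cox fit (exponential survival, hyposmia median 20.9 months from the pilot, censoring at 24 months) gave 0.46, 0.49 and 0.53, so the approximation is adequate.

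**3. What that would mean for power**

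The mean of the planned event rates, 47% and 53%, is 50%, so 64 patients give about 32 events. Schoenfeld power, two-sided 5%, equal groups, is Φ(√(32 × 0.25) × |ln HR| − 1.96).

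- HR 0.43: Φ(2.828 × 0.844 − 1.96) = Φ(0.43) = 67%
- With the simulated HRs for s = 10%, 20% and 30%: 59%, 51% and 43%

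The starting value is already below the stated 80%. That is a separate matter, on which this point does not rest.

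**4. Direction**

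In the formula, r = 1 leaves 0.43 unchanged and r > 1 moves the HR further from 1. Surgical involvement could accompany a wider resection (better survival, smaller r) or an unfavourable site (worse survival, larger r). The article does not settle which.

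**The case against.** **Silence in a condensed article.** The full protocol and the MRI reading form are not shown, all scans are read by both radiologists, and Study cohort and Statistics use the broader term involvement. A reader might infer that the form certainly has no surgical item. The text does not go that far. It does, however, state the MRI item, the scan used, the mechanisms and the covariates, and surgical injury is in none of them. Stratification, MRI and the Sample size section all describe the item as infiltration. The point stands for the plan as stated.

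**No evidence that it happens.** A reader might infer that operation-caused hyposmia is in fact being counted as the disease marker. No section shows that any patient has it. Table 2 does not require a resection, and extent of resection evidently varies. This objection stands: the point is a gap in what can be ruled out, not a demonstrated error.

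**The primary question is prognostic.** If postoperative smell is the marker, a surgical contribution is part of it. This largely stands, and it moves the weight of the point to the mechanistic aim. The hypothesis also introduces its external causes as examples, so the list is not closed. But an open list makes it more necessary, not less, to consider surgery before concluding that the cause is intrinsic.

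**The figures may double-count.** A reader might infer that the planned HR will be diluted by 7% to 22%. The pilot tested its patients at various time points, and nothing says that this was before surgery. If pilot testing was also postoperative, 0.43 already contains any surgical component. This stands in full.

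**Conclusion.** The point holds as a limit on the mechanistic conclusion. As the plan is stated, hyposmia from surgical injury cannot be told apart from hyposmia without infiltration, so that pattern alone cannot support the claim that the dysfunction is intrinsic.

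The number of patients affected is unknown. For overall survival the consequence is smaller and its direction is not fixed. The range of 0.46 to 0.52 rests on three assumptions that the article does not support: shares of 10% to 30%, surgical cases carrying the normosmia hazard, and a pilot HR free of surgical hyposmia. It shows the scale of a possible effect and is not an estimate of bias.

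**What to change.** **Coding.** Add one item for both existing readers: does resection cavity, haemorrhage or ischaemia involve any of the olfactory structures listed in the Introduction? Record it by side, separately from tumour infiltration. Use the early scan ("Postoperative (24 h-72 h post surgery"), or the post-radiotherapy coronal T2 where the early scan lacks the resolution. Because each nostril is tested separately for identification, side-coded involvement can be set against side-specific scores.

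**Analysis.** Prespecify a sensitivity analysis that adjusts for, or leaves out, patients with surgical involvement. Apply it chiefly to the comparison of hyposmia without infiltration and secondarily to overall survival. Make the Statistics covariate list agree with the Sample size section on extent of resection.

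**Interpretation.** State in advance that a conclusion of intrinsic dysfunction is limited to what remains once surgical involvement is accounted for.

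**Cost.** No new visit or reader is needed, and the scans are already part of routine care. Scans of patients already enrolled (32 by April 2025) must be re-read. Coding may be coarser on routine early sequences, since the article ties the high-resolution coronal T2 to the post-radiotherapy reading. With 64 patients the sensitivity analysis will be imprecise and should be reported with its interval rather than as a test.

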In a previous study, we demonstrated that patients with glioblastoma are significantly more prone to olfactory dysfunction than a control group of patients with non-tumorous neurological diseases not primarily associated with smell impairment [12]. The study demonstrated the prognostic relevance of an olfactory dysfunction in glioblastoma patients regardless of the olfactory tract affection by the tumor. We studied 122 patients (73 glioblastoma patients and 49 controls). All were tested at various time points using the Sniffin Sticks screening test—a 12-odor test where participants identify each odor from four predefined options. Normosmia was defined as a Sniffin Sticks score (SSC) of 9.9 or higher [10]. Patients scoring below 10 were classified as the hyposmia group (HG), while those scoring 10 or higher were classified as the normosmia group (NG) [12]. After the initial examination, 34 glioblastoma patients were assigned to the HG and 39 to the NG. O6-Methylguanine-DNA Methyltransferase (MGMT) promoter methylation, age, sex, Karnofsky performance status (KPS), tumor histology, and extent of resection did not differ significantly between the two groups. Glioblastoma patients scored significantly lower on the smell test than controls (mean SSC 8.9 vs. 9.9, *p* = 0.003). Even patients tested before chemotherapy or radiotherapy onset performed worse than controls (mean SSC 8.2 vs. 9.9, *p* = 0.001). MRI was used to determine if tumor growth affected primary olfactory centers (ethmoid bone, olfactory groove, or temporomesial structures like the posterior orbitofrontal cortex, uncus, anterior parahippocampal gyrus, entorhinal area, insula, or amygdala). The median overall survival (OS) of the cohort was 28.1 months, and the median progression-free survival (PFS) was 14 months. Patients in the HG had worse OS (20.9 vs. 40.6 months, *p* = 0.035) and PFS (9 vs. 19 months, *p* = 0.022) compared to NG.

In our previous study, longitudinal analysis was hampered by limited re-examinations during follow-up (n = 32). Only some patients were assessed before chemoradiotherapy (n = 15), restricting our ability to evaluate neurotoxicity from radio- and chemotherapy. Additionally, the HG was older, had lower MGMT promoter methylation rates, and a lower KPS than the normosmia group—differences that, though not statistically significant, are crucial in ensuring that the groups were not distributed exactly equally, which led to criticism from readership.

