#### Stratification

Stratification will be performed once during the visit 1 (after radiotherapy), when, among other factors, the patient's MGMT promoter methylation status and group assignment (NG vs. HG) are determined. Additionally, the post-radiotherapy MRI of the skull will be assessed for infiltration of the olfactory tracts. Stratification may result in the exclusion of study participants after visit 1 (see Table 1).

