### Statistics

A Cox proportional hazards regression model will be used to describe the event, overall survival, where the variables MGMT, KPS, age, MRI findings of olfactory tract involvement and olfactory function will be used as the covariates. All models will be check for proportionality and the log likelihood will be used as the criteria for model selection. All statistical analysis and graphics will be conducted in R version 3.5.0 (Boston, MA).

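### Tying the baseline visit to the MGMT result can cost a patient the only full pre-radiotherapy assessment, although MGMT is not used before visit 1

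*Protocol article*

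**What the plan says.** The Study visits section gives each pre-radiotherapy visit its own trigger. The first is "screening (postoperative, once histology is available"), which needs no MGMT result. The second is "baseline (as soon as MGMT promoter methylation status is determined, but before radiotherapy"), which needs one and also has a deadline.

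Table 2 defines the tumor criterion as "Newly-diagnosed glioblastoma (CNS WHO 2021; IDH wild-type) before start of first radiotherapy" and has no MGMT item. MGMT has two stated uses. One is stratification: "Stratification will be performed once during the visit 1 (after radiotherapy), when, among other factors, the patient's MGMT promoter methylation status and group assignment" are established. The other is the Cox model, "where the variables MGMT, KPS, age, MRI findings of olfactory tract involvement and olfactory function will be used as the covariates".

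On olfaction, screening includes the identification test only; "At subsequent visits, both threshold and identification modules are done". The sections on quality of life, neurocognitive testing and biobank sampling each leave out screening, so these start at baseline.

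**The concern.** A visit whose opening depends on a laboratory result and whose closing depends on the start of treatment can have an empty window. That happens whenever the result comes after treatment has begun. The article gives no alternative trigger for this case.

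What is lost cannot be recovered, because the next visit is about 4 weeks after radiotherapy ends. The Perspective section wants to separate treatment-related neurotoxicity from an effect of the disease itself, using identification and threshold tests together with repeated cognitive and quality-of-life measures. For every one of these except identification, baseline is the only pre-radiotherapy value. The condition that puts it at risk serves no stated purpose at that visit.

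**Working it through.** The plan gives no figure on this point, so the check sets its sections side by side. A short calculation then bounds the possible size.

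**1. Can the two conditions conflict?** Baseline opens when MGMT is determined and closes when radiotherapy starts.
- Result before radiotherapy: the window exists, though a late result shortens it.
- Result after radiotherapy starts, or never: the window is empty.

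Screening needs histology only, so a patient can be consented, screened and eligible and still have no permissible baseline date.

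**2. Is MGMT needed at baseline?** It is not in Table 2. Study cohort and Stratification place its first use at visit 1 (4 ± 1 weeks after radiotherapy ends). Sample size and Statistics use it as a covariate in the final model. No section uses it between screening and visit 1.

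**3. Do the sections agree on when MGMT is known?** Study visits requires it before baseline. Stratification describes visit 1 as the time when "MGMT promoter methylation status and group assignment (NG vs. HG) are determined". This may mean only that both are established by then, since group assignment rests on the screening test. The two statements should still be aligned.

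**4. What is measured before radiotherapy?**

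| Measure | Screening | Baseline |
|---|---|---|
| Identification test | yes | yes |
| Threshold test | no | yes |
| Neurocognitive battery | no | yes |
| EORTC quality of life | no | yes |
| Biobank blood | no | yes |

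Psychosomatic testing is left out of the table because Table 1 marks it at screening while its own section excludes screening.

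A patient without baseline therefore loses the last four rows and keeps the first.

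**5. How large could the loss be?** The article gives no MGMT turnaround time, failure rate or interval to radiotherapy. Let f be the assumed share of the 64 patients with no result before radiotherapy, so that n = 64 × (1 − f) have a baseline. The detectable standardized paired change at 80% power and two-sided 5% is (1.960 + 0.842)/√n.

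| f (assumed) | Without baseline | n | Detectable change (SD) |
|---|---|---|---|
| 0% | 0 | 64 | 0.35 |
| 5% | 3 | 61 | 0.36 |
| 10% | 6 | 58 | 0.37 |
| 15% | 10 | 54 | 0.38 |
| 20% | 13 | 51 | 0.39 |
| 30% | 19 | 45 | 0.42 |

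The calculation counts only losses from this rule and ignores death and dropout. Precision suffers little across the plausible part of the range.

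**The case against.** The strongest reply is that this is scheduling language with radiotherapy as the outer limit. Nothing declares a patient ineligible or withdrawn if MGMT is pending, and the full protocol, which the article condenses, may contain a fallback. It is also reasonable to hold back a long test battery until a required stratification factor is known, since stratification can exclude patients after visit 1. This stands in part. It is a reason not to call MGMT a hidden eligibility criterion. It does not remove the conflict, because the article itself states a trigger and a deadline that can be incompatible. Nor does the current rule spare effort reliably: exclusion at visit 1 also depends on MRI findings that are not available until after radiotherapy.

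A reader might also infer that a patient without baseline drops out of the neurotoxicity comparison altogether. The documents do not support that. The screening identification test falls after surgery and, by Table 2, before radiotherapy and without prior chemotherapy. It can be compared with later identification scores.

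For the same reason the rule does not simply recreate the previous study's weakness: "Only some patients were assessed before chemoradiotherapy (n = 15), restricting our ability to evaluate neurotoxicity from radio- and chemotherapy". That study used the 12-odor identification test only, and screening now supplies that test before treatment.

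**Conclusion.** The concern holds in a limited form. Read literally, the baseline rule leaves a patient whose MGMT result is pending at the start of radiotherapy with no permissible visit. It thereby forfeits the threshold, neurocognitive, quality-of-life and biobank values from before radiotherapy. Group assignment and the primary survival comparison are unaffected, because they rest on the screening identification score.

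Severity is minor, since only secondary longitudinal aims are touched. The frequency is unknown, and the 3 to 10 patients rest on an assumed 5 to 15%. The argument is that the missing values are avoidable and unrecoverable; lost power is not the issue.

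It is tempting to add that the loss is selective, for instance that late or failed MGMT results are commoner after biopsy alone and would tilt the longitudinal set towards resected patients. The document gives no data linking MGMT availability to extent of resection, so no claim of bias is made.

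**What to change.** Three edits to the text:

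1. In Study visits, define baseline as a visit after screening and before the first radiotherapy fraction, held whether or not the MGMT result is available.
2. Require the MGMT result by visit 1, where stratification uses it.
3. Reword the Stratification section so that it agrees with Study visits on when MGMT status is known.

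The handling of patients whose MGMT status is never determined belongs to the stratification rule and the analysis plan. Moving baseline does not settle it.

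The cost is a sentence or two, with no added visit, test or patient. Some patients would complete the baseline battery before MGMT is known and might later be excluded at stratification, but the current schedule already allows exclusion after baseline. According to Results, 32 of the 64 patients had been recruited by April 2025 and enrollment is planned to run to December 2026, so at that date the change could still help the remaining 64 − 32 = 32.

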#### Disease status (progression)/Survival data

Disease status regarding progression and overall survival will be recorded at each visit.

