## Results

The first participant was enrolled in May 2023. As of April 2025, 32 patients and 9 controls have been recruited. A second study center opened at Münster University Hospital in December 2024, and more centers may be added, aiming to complete enrollment by December 2026. Follow-up will continue until December 2028, with final results of the observational study expected in 2028. Additional translational projects involving biomaterials are planned, and their study protocols are currently under development.

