### Perspective

This prospective, multicenter observational study aims to clarify the prognostic significance and underlying mechanisms of olfactory dysfunction in newly diagnosed glioblastoma. Previous retrospective data have suggested an association between impaired olfaction and reduced survival in glioblastoma patients [12], but those findings were limited by potential confounders and lacked longitudinal follow-up. This study was designed to overcome these limitations by integrating rigorous stratification, serial olfactory testing, multimodal imaging, neurocognitive assessments, and molecular profiling.

The primary objective is to determine whether olfactory dysfunction independently predicts overall survival when accounting for established prognostic factors such as MGMT promoter methylation, KPS, age, and extent of resection. In parallel, two mechanistic hypotheses are tested: (1) direct tumor invasion of olfactory-related structures, and (2) neurotoxicity resulting from radiotherapy or chemotherapy. The aim is to prove that an olfactory dysfunction in glioblastoma is intrinsic to the disease and is not caused by radiochemotherapy or local tumor infiltration in the olfactory tract.

To assess structural involvement, high-resolution coronal T2-weighted MRI and DTI are employed to detect infiltration of primary and secondary olfactory regions. Metabolic activity in these areas is further evaluated using FET PET in clinically indicated cases. These imaging data are assessed independently by two neuroradiologists to ensure objective interpretation.

To investigate treatment-related neurotoxicity, olfactory function is longitudinally monitored over two years using both identification and threshold components of the Sniffin’ Sticks test. These data are complemented by repeated neurocognitive testing, and quality of life assessments, allowing for correlation between sensory decline, cognitive function, and psychosocial burden.

The study incorporates matched healthy controls to provide normative data and differentiate disease-specific patterns from age-related olfactory decline. Additionally, tumor genome sequencing and biobanking enable exploratory analyses of molecular correlates of hyposmia and clinical outcome.

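### Survival recording is tied to visits with an undefined two-year limit, and the visit schedule does not fit the December 2028 close; if survival capture ends with the visits, about a tenth to a quarter of obtainable deaths are lost

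*Protocol article*

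**What the plan says.** All places are in the protocol article.

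- **Study visits.** The schedule counts from the end of radiotherapy: "visit 4 (12 months ± 2 weeks after end of radiotherapy"), then "follow-up visits (every 6 months ± 2 weeks after visit 4, for a maximum of 2 years").
- **Disease status (progression)/Survival data.** "Disease status regarding progression and overall survival will be recorded at each visit". Table 1 agrees: survival is a visit item from baseline to the follow-up visits.
- **MRI.** Scans after radiotherapy are at "approximately 3, 6, 12, 18, and 24 months after radiotherapy", apart from the one at about four weeks.
- **Perspective.** "olfactory function is longitudinally monitored over two years".
- **Results.** "The first participant was enrolled in May 2023". The sponsor is "aiming to complete enrollment by December 2026". "Follow-up will continue until December 2028, with final results of the observational study expected in 2028".
- **Obtaining informed consent.** Consent is taken at screening, which comes after surgery and before radiotherapy.
- **Sample size calculation.** Event rates are planned over two years, with a hazard ratio of 0.43, 5% significance and 80% power.

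**The concern.** Three statements bear on how long a patient contributes to the primary endpoint, and they do not fit together: a visit limit with no stated origin, survival recorded at visits, and follow-up to a calendar date. A patient enrolled in May 2023 could be observed for more than five years by December 2028. Under the visit limit the same patient would be observed for about two or three years after radiotherapy. These are different censoring rules. The pilot median in the normosmia group was 40.6 months, beyond the 24-month limit and about at the end of the 36-month one, so the choice decides how many deaths in that group are seen.

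Deaths are the scarce quantity in a 64-patient study. Longer survival follow-up adds deaths without adding patients. The calendar is a separate difficulty, because the last patients cannot finish the schedule before the stated close.

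**Working it through.** **The plan's own figure.** For a hazard ratio of 0.43, two-sided 5% (sidedness is not stated) and 80% power, Schoenfeld's formula needs 4 × (1.960 + 0.842)² / (ln 0.43)² = 44.1, so 45 deaths. At the planned average two-year event rate of 50%, 64 patients give 64 × 0.50 = 32 deaths and about 67% power. The stated sample size therefore does not reproduce. That is a separate matter, but it shows what each death is worth.

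**Calendar.** Inputs: accrual May 2023 to December 2026 (43 months, taken as uniform) and close 24 months later. The gap g from enrolment to end of radiotherapy is not given; I assume 1.5 to 4 months.

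- 24-month reading: patients enrolled in the last g months cannot reach the final visit. 64 × 1.5/43 = 2.2; 64 × 4/43 = 6.0. So about 2 to 6 patients.
- 36-month reading: 64 × (12 + 1.5)/43 = 20.1; 64 × (12 + 4)/43 = 23.8. So about 20 to 24 patients.
- If 32 patients entered by April 2025 and 32 afterwards, the counts are 2.4 to 6.4 and 21.6 to 25.6. Using the two-week visit window removes less than one patient.

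**Deaths.** Assumptions: exponential survival from enrolment at the pilot medians (20.9 months hyposmia, 40.6 normosmia), 32 patients per group, no exclusions at visit 1, no loss to follow-up, g = 2 to 4 months. Death probability by time t is 1 − 2^(−t/median). Time from enrolment to December 2028 is uniform on 24 to 67 months.

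- All followed to December 2028: average probabilities 0.760 and 0.530, so 32 × (0.760 + 0.530) = 41.3 deaths.
- Limit of 24 months after radiotherapy: for g = 2, 0.577 and 0.358, so 29.9 deaths; for g = 4, 0.602 and 0.378, so 31.4 deaths. Loss: 1 − 29.9/41.3 = 28%; 1 − 31.4/41.3 = 24%.
- Limit of 36 months after radiotherapy, also cut at December 2028: 36.7 to 37.4 deaths. Loss: 11% to 9%.

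**Power.** Φ(√d × |ln HR|/2 − 1.96), where d is the number of deaths and |ln 0.43|/2 = 0.422.

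| Survival capture | Deaths | Power, HR 0.43 | Power, HR 0.515 |
|---|---|---|---|
| To December 2028 | 41.3 | 77% | 57% |
| 36 months after radiotherapy | 36.7-37.4 | 72-73% | 52-53% |
| 24 months after radiotherapy | 29.9-31.4 | 64-66% | 44-46% |

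The last column uses the ratio that the pilot medians imply under exponential survival, 20.9/40.6 = 0.515. It is the internally consistent companion to the death counts, and its levels are clearly lower.

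**Sensitivity.** With 50% dead at two years, as the plan averages, follow-up to December 2028 gives 45.8 deaths. The 24-month limit gives 33.8 to 35.3 (23-26% lost) and the 36-month limit 41.0 to 41.8 (9-10% lost). Over the 12 to 48 month range of medians in the Introduction, with g from 0 to 4 months, the loss is 12-38% on the 24-month reading and 3-18% on the 36-month reading.

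**The case against.** The strongest reply is that the article limits visits, not ascertainment of death. Recording survival at each visit sets a minimum. Follow-up to December 2028 may well include vital status, and a condensed article may leave calls, registries and censoring rules to the full protocol. This stands as far as it goes. A reader might infer that survival is captured only at visits and later deaths are discarded, but the article says neither, so the loss above is conditional.

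A reader might also put the loss at a third. That needs the two years to run from enrolment (28.3 deaths, 31% lost), whereas the visit schedule counts from the end of radiotherapy.

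A third tempting inference is informative censoring, with survival biased upward in sicker patients. It requires that a patient who misses a visit gets no death date, and no passage says so.

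It is also fair that a two-year horizon matches the sample-size assumption, that administrative censoring at study close is ordinary in a Cox analysis, and that the two effects trade off. The 24-month reading loses more deaths but leaves few patients short of the last visit; the 36-month reading does the reverse.

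The undefined origin of the two years and the dates that do not close remain after all of this. Both are in the current text and do not depend on what the full protocol adds.

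**Conclusion.** The point holds as a badly fixed follow-up rule for the primary endpoint. The two-year limit has no stated origin: the MRI and Perspective sections favour 24 months after radiotherapy, and the wording after visit 4 allows 36. On either reading the last enrolled patients cannot complete the schedule by December 2028, and final results in 2028 hardly fit follow-up that runs to the end of that year.

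If survival capture stops with the visits, the cost is about 10 to 11 deaths and 12 to 14 points of power on the 24-month reading, or about 4 to 5 deaths and 4 to 5 points on the 36-month reading, at a hazard ratio of 0.43. These figures rest on exponential survival at the pilot medians, equal groups, uniform accrual, no exclusions or losses, and an assumed 2 to 4 month gap to the end of radiotherapy. At the pilot medians, even full follow-up to December 2028 yields about 41 deaths, short of the 45 needed for 80% power. The sample size remains the larger problem.

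**What to change.** - State from which date the two years run, and make the visit, MRI and Perspective sections agree.
- Keep the visit schedule for the other assessments. Collect vital status and date of death for every patient retained after visit 1 to one common cut-off, independent of visit attendance (telephone, treating physician or registry).
- Censor survival at the date last known alive, or administratively at the cut-off.
- Set the cut-off at or after the last patient's final visit and the results date after that. With enrolment to the end of December 2026 and a gap of 1.5 to 4 months, the 24-month visit falls between mid-February and the end of April 2029; on the 36-month reading, one year later.

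The cost is one vital-status sweep, an amendment with consent wording, and a somewhat later results date. No patients are added. If the full protocol already provides for survival follow-up to a common date, a clarifying sentence settles that part, and only the origin of the limit and the dates need correcting.
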